#### Blinding

Older participants, interviewers performing the baseline assessment and researchers doing the outcome assessment and data analysis will be blinded to group allocation. It won’t be possible to blind the research coordinator and municipal health and social care professionals performing the intervention to group allocation. Interviewers won’t be blinded when doing the follow-up.

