**Methods/design:**

The study is a prospective, longitudinal randomized four-armed controlled trial with follow-up at 6 months. The study group aims to include 900 community-dwelling older adults aged 60 years and over from 3 municipalities in Flanders (Belgium). While selecting the study group, risk profiles for frailty will be taken into account. Participants will be randomly selected from the census records in each municipality. Data will be collected prospectively at baseline (T0) and at follow-up, 6 months after baseline (T1). At baseline, participants who are at least mild frail on one of the 5 domains of frailty (CFAI-plus) or feel frail based on the subjective assessment of frailty will be randomly assigned to (1) the study group or (2) the control group. A mixed method design with the inclusion of quantitative and qualitative data analyses will be used to evaluate the efficacy and experiences of the detection and prevention program on frailty.

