**Fig. 1 Fig1:**
[figure not shown]
Flow diagram of the D-SCOPE frailty program

Older adults who are at least mild frail on one of the 5 domains of frailty (CFAI-plus) or feel frail based on the subjective assessment of frailty will be randomly assigned to either (1) the experimental group or (2) the control group. Older adults with no-to-low frailty (CFAI-plus) or who do not feel frail (subjective assessment of frailty) will be grouped into a third group. A fourth group will include frail older adults willing to participate in the T0 and T1 assessment but not in the intervention part. All groups except for the experimental group will receive care as usual.

All older participants will be assessed after a 6 months’ period. The study will include an effect evaluation and a process evaluation of the RCT. The effect study will be conducted using a quantitative evaluation of the outcome measures for frail community-dwelling older adults. The process evaluation will be performed by a quantitative monitoring of the experimental group (including follow-up telephone interviews) and qualitative focus groups with older adults, informal caregivers and municipal health and social care professionals in each municipality.

The baseline assessment T0 will begin in June 2017 until October 2017. The study assessment T1 will begin in December 2017 until April 2018. The intervention will take place between June 2017 and March 2018, between the baseline assessment T0 and the study assessment T1. The qualitative evaluation will take place in March and April 2018. The data analysis will take place between April 2018 and June 2018.

The content of the program has been developed in close collaboration with representatives of different home care and support levels, i.e. general practitioners, home care organizations, social service of the municipalities, home nurses, older people’s organizations, centers of expertise in housing and care, care insurances companies, universities, etc.

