### Participants and eligibility criteria

Study participants will be community-dwelling older adults aged 60 years and over. In order to explore the most efficient selection strategy to detect frail older adults, two randomized selections, with replacement addresses, from the census records will take place in each municipality. Each randomized selection in each municipality will include 150 participants. The two stratified samples will be based on previous research on risk profiles for frailty [29]**.** Risk characteristics for frailty are gender, age, marital status, moved in the past 10 years and migration background. In the first sample (*n* = 450) older participants will need to fulfill at least one criterion. This implies that the participants will be women or aged 70 years and over or not have a partner or have moved in the past 10 years or will have a migration background. In the second sample (*n* = 450) all older participants will need to fulfill all selection criteria. This implies that older participants will be aged 70 years and over, have no partner, and moved last 10 years. The second sample will exclude the variable migration background due to too small samples within the three selected municipalities.

Exclusion criteria will be current hospitalization, institutionalization, when the older participant himself or his/her informal caregiver indicates that the older participant is not able to participate or if the interviewer notes that the older participant is cognitively not capable to provide adequate answers.

Older adults will be included in the RCT if they are at least mild frail on one of the 5 domains of the CFAI-plus (i.e., ≥ 25 for physical frailty, ≥ 12.52 for cognitive frailty, ≥ 20 for psychological frailty, ≥ 37.5 for social frailty and ≥ 5 for environmental frailty) or feel frail based on the subjective assessment of frailty (i.e. at least agree with the statement), and accept to participate in the intervention.

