### Intervention

The intervention contains several steps in order to empower older adults and improving their access to care and support [28]. Older participants assigned to the experimental group after the first home visit containing the T0 baseline assessment will be contacted by a professional from the social service of the municipality for a second home visit. These professionals will already be experienced with conducting home visits and will receive training and instructions concerning multidimensional frailty, frailty-balance and taking into account the strengths and competences of older adults and their informal caregivers. During the second home visit, the professional from the social service of the municipality will further explore the older adult’s competences, needs and preferences. Based on the results of the baseline assessment and on the results of the second home visit, the professional from the social service of the municipality will propose a type of intervention. The decision and organization of tailored care and support will be made together with the older participant and his/her environment. The older participant will be accompanied in the referral once decided in which organization/form of intervention the older participant will participate in order to reduce dropout. The older participant will receive tailored care and support whereby his competences, strengths and resources will be supported [30]. The intervention will depend on the availability of the care and support services in the municipality, and could be formal (e.g., home care) or informal (e.g., activities of an older adult’s association). A professional from the social service of the municipality will monitor which care the participant receives, when the older person cancels the care and support and if everything is going according to his/her wishes. This will be done monthly by telephone.

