#### Data gathering

Data on baseline characteristics, frailty, balancing factors and outcomes will be collected to evaluate the effect of the intervention with questionnaires at two points in time: T0 and T1 (6 months after inclusion). Participants in the study will concern all groups; the experimental group of the RCT, the control group of the RCT, older participants with no-to-low frailty (CFAI-plus) or who do not feel frail (subjective assessment of frailty) and care avoiders. Trained volunteers or researchers will collect the T0 data. A professional from the social service of the municipality will receive all completed questionnaires and informed consents from the baseline assessment after the first home visit and will register the completed questionnaires in a specific designed computer program named Qualtrics. The research coordinator, who is responsible for the randomization to the control and experimental group, will be the person who can consult the results and will communicate to the municipality which respondents are randomized in the experimental group. The municipality will arrange that the experimental group receives a second home visit by a professional from the social service of the municipality, search an appropriate intervention and do the follow-up. After 6 months, trained volunteers and researchers will collect the T1 data. A professional from the social service of the municipality will again receive all completed questionnaires from the T1 assessment and will register them in the specific designed computer file. At the end, the research coordinator will consult the data.

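### The Blinding section claims blinding of participants that the design rules out, and of outcome assessment that its own last sentence appears to withdraw

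*Protocol article*

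**What the plan says.** The Blinding section of the protocol article makes three statements.

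- It lists who is blinded: "Older participants, interviewers performing the baseline assessment and researchers doing the outcome assessment and data analysis will be blinded to group allocation".
- It says that blinding is not possible for the research coordinator and for the municipal professionals who deliver the intervention.
- It ends: "Interviewers won’t be blinded when doing the follow-up".

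Other sections describe what happens around T1 and in each arm.

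- Abstract, Methods/design: data are collected at baseline and "at follow-up, 6 months after baseline (T1").
- Data gathering: "After 6 months, trained volunteers and researchers will collect the T1 data". A municipal social-service professional then receives and registers the completed T1 questionnaires, and the research coordinator consults the data.
- Participants and eligibility criteria: frail older adults enter the RCT if they meet a frailty criterion "and accept to participate in the intervention".
- Intervention: experimental participants "will be contacted by a professional from the social service of the municipality for a second home visit". Care is then decided jointly, the referral is accompanied, and the care received is monitored: "This will be done monthly by telephone".
- Study design, text under Fig. 1: "All groups except for the experimental group will receive care as usual".

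**The concern.** Two properties are claimed that the rest of the article does not bear out: that participants do not know their arm, and that those who assess the outcome do not know it either.

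This matters because of the type of outcome. All six primary outcomes are the participant's own answers to questionnaire items, and the article describes no separate rating or adjudication step. Quality of life and community inclusion each use one item, and ageing well in place uses one self-constructed question. The other three are multi-item: meaning in life has 5 items, mastery has 4 plus 1, and life satisfaction uses a validated scale. With outcomes of this kind the participant is in effect the assessor, and the interviewer is the only other person who can influence the answer. If both know the allocation, response bias and detection bias are open on every primary outcome. A reader relying on the first sentence of the Blinding section would think otherwise.

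**Working it through.** The check is mainly a comparison of statements. The plan gives no figure to reproduce.

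**Participants**

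1. Before randomization they are told the purpose and conduct of the study (Study design) and must accept the intervention (eligibility criteria). They therefore know that an intervention exists.
2. After randomization the experimental arm gets a second home visit by a municipal professional, a jointly decided care plan, accompanied referral and monthly telephone monitoring (Intervention). Table 2 marks the intervention, the quantitative monitoring and the monthly follow-up for the experimental group only.
3. The control arm gets usual care. No sham visit or attention control is described.
4. Someone who agreed to an intervention and then receives it, or does not, can tell which arm they are in. The participant claim is incompatible with steps 1 to 3.

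**Outcome assessment**

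1. The primary outcomes are questionnaire answers (Primary outcome measures; Table 2 places them at T0 and T1).
2. T1 is collected by trained volunteers and researchers (Data gathering), so the T1 interview is where the outcome is assessed.
3. The abstract uses follow-up for T1. Interviewers who are unblinded at follow-up are then unblinded at the outcome assessment.
4. That conflicts with the earlier statement that researchers doing the outcome assessment are blinded.

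**What remains of the claim**

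Baseline interviewers are blind in any case, because randomization comes after the baseline assessment (Randomization). Apart from them, only data analysts are left. For analysts, Data gathering raises a further question. The T1 questionnaires are registered by municipal professionals, the staff group that delivers the intervention, and are then consulted by the coordinator. The Blinding section says that neither can be blinded.

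**Size**

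No size can be derived. The article gives no per-arm number for this trial, since its 900 participants cover four groups, and it gives no basis for a bias value. The following is an illustration under assumptions only. Take 198 per arm (220 × 0.9; both the 220 and the 10% loss are another study's figures, reported under Power analysis), no true effect, and a systematic bias of b SD. A two-sided 5% t-test then has noncentrality δ = b × √(198/2) = 9.95b on 394 degrees of freedom.

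| Assumed b | δ | Rejection rate |
|---|---|---|
| 0.05 | 0.50 | 0.079 |
| 0.10 | 0.99 | 0.168 |
| 0.15 | 1.49 | 0.319 |

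These figures show how a t-test reacts to bias. They do not estimate this trial's error rate or what better masking would gain, because they do not separate interviewer bias from participants' response bias.

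**The case against.** The strongest reply concerns the assessor part. The article also uses follow-up for the municipality's monitoring: Data gathering has the municipality do the follow-up, and Study design mentions telephone interviews at follow-up. The researchers who assess outcomes could also be staff who score and analyse, as distinct from interviewers. On either reading the wording is ambiguous but not contradictory.

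This has some force, and it is why the assessor part is stated less firmly. It is still the weaker reading. The Intervention section gives the monthly calls to municipal professionals, whom the Blinding section has already listed as unblinded, so its last sentence would be redundant. Data gathering has researchers among those who collect T1. Neither reading helps the participant claim. The consent text is not shown, so what controls are told about their arm is unknown, but the difference in contact between the arms is plain from the article.

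Three stronger inferences are tempting, and the document does not support them.

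- A reader might infer that the trial will conceal an unblinded assessment. It will not necessarily do so: the same section openly says that interviewers are unblinded at follow-up. The fault is inconsistent wording.
- A reader might infer that the interviewers' unblinding is needless. The article gives no reason for it, and T1 collection is not assigned to the staff who deliver the intervention. But T1 asks about 7 informal and 13 formal caregivers, so the arm may emerge in the interview itself. How much is avoidable is not known.
- A reader might infer that the same individuals interview at T0 and T1. Data gathering names roles, not persons.

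**Conclusion.** The Blinding section is wrong as written. The participant claim is incompatible with the design, and this does not depend on how any term is read. The outcome-assessment claim contradicts the section's last sentence on the natural reading that follow-up means T1; that part rests on the reading. Since every primary outcome is self-reported, the trial should be described as open to response bias and, at T1, to detection bias. The magnitude is not estimable from the document. The rejection rates shown above depend on an assumed 198 per arm and assumed biases of 0.05 to 0.15 SD, and the conclusion does not rely on them.

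**What to change.** **Required (wording).** Rewrite the Blinding section to state that participants, intervention staff and the research coordinator are not blinded. Limit the blinding claim to baseline interviewers and to analysts who work with masked arm labels. State plainly whether T1 interviewers know the allocation, and give response and detection bias on the self-reported primary outcomes as a limitation.

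**Required (consistency).** Reconcile the section with Data gathering, where municipal professionals register the T1 questionnaires and the unblinded coordinator consults the data. Say how the analysts' masked data set is produced from there.

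**Recommended (conduct).** Do not tell T1 interviewers the allocation. Ask the primary-outcome items before the items on care received; the article does not give the T1 item order, so this may already be the case. Have each interviewer record whether they became unblinded, and when. This changes a stated design choice, so it is an improvement and not a correction of an error.

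**Cost.** The required part is text, plus a masking step in data handling. The recommended part is an interviewer instruction, possibly a reordering of the questionnaire, and one extra recorded item. Whether it needs more staff time cannot be judged from the article. Some participants will still reveal their arm, and no interviewer masking removes the response bias of participants who know what they received.

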### Analysis of the data

#### Effect evaluation

The experimental and control groups will be described at both time points with descriptive statistics. Similarity of characteristics between the two groups will be assessed by means of independent sample t-tests or chi-square tests. Differences in measurements between T0 and T1 will be assessed by means of repeated measures ANOVA’s. In order to explore which combination of resources lead to a higher quality of life, meaning in life, life satisfaction, mastery, community inclusion and ageing well in place in frail community-dwelling older adults, different interaction models with balancing factors as moderators will be tested. We will explore which balancing factors are moderators for having a good quality of life, meaning in life, life satisfaction, mastery, community inclusion and ageing well in place, despite being frail. We will explore the hypothesis that frail older adults who have the adequate resources (positive frailty-balance) have a better chance for aforementioned positive outcomes than frail older adults with a negative frailty-balance. For each measure, regression analyses will be performed with the T1 scores as the dependent variable, the research group (experimental vs. control) as independent variable of interest, and demographic variables and differences in baseline characteristics as co-variates. Multivariate analyses will be performed in order to answer the research questions.

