### Randomization

Eligible participants will be randomly assigned directly after the baseline assessment by the principal researcher, using computer-generated randomization to either the control or the experimental group.

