#### Power analysis

As we have no clear view yet on all aspects, factors, scales, outcomes, statistical analyses, etc., it is not feasible to run detailed power analyses a priori. However, according to Cohen [64] and when using the online a priori sample size calculator for independent sample t-tests [65]; the minimum sample size per group (experimental as well as control group) with a probability level of .05, an anticipated Cohen’s d effect size of 0.5 (medium) and a desired statistical power of 0.8 will be 64. To find differences with a small effect size (cohen’s d = 0.2) between the 2 groups a total n of 788 (394 in each group) is required.

As is our longitudinal design is concerned, we have based our a priori estimation on a study of Fabricotti et al. [66]. They expect a 10% loss to follow up (due to mortality, re-housing, impossibility or unwillingness to participate further) between T0 and T1. By including 220 older adults in both the experimental and control group, they state that their sample is sufficient to detect changes. Assuming an average effect size of 0.5 and significance of 5%, this gives a power of 0.997. They further argue that if a small effect size is expected of 0.3 with a significance of 5%, this still supplies sufficient power at 0.837. Interfering variables will also play a role. At an average effect size (f2) of 0.15 and significance of 5%, assuming five independent variables, the power is 0.97. Even with 15 independent variables, the power remains sufficient at 0.856.

So, in sum, it was decided to aim for 900 community-dwelling older adults aged 60 years, equally divided over the municipalities Knokke-Heist, Ghent and Tienen in Flanders, Belgium; so 300 community-dwelling older adults will participate in each municipality.

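### Beyond demographics, the T1 regression picks covariates by observed baseline differences and does not fix the T0 score of the same outcome as a covariate

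*Protocol article*

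**What the plan says.** The article's effect-evaluation paragraph, under Analysis of the data, sets out three steps for the two randomised arms.

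- Baseline comparison: "Similarity of characteristics between the two groups will be assessed by means of independent sample t-tests or chi-square tests".
- Change over time: "Differences in measurements between T0 and T1 will be assessed by means of repeated measures" ANOVAs.
- Effect regression, for each measure: T1 score on arm, with "demographic variables and differences in baseline characteristics as co-variates".

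The T0 score of the outcome is not named in the regression. Table 2 and the Data gathering section show all six primary outcomes collected at both T0 and T1. The Randomization section places allocation directly after the baseline assessment, so the T0 score is a proper pre-randomisation covariate. The Additional measures section lists the socio-demographic variables: age, gender, country of birth, educational level, marital status and a move in the last 10 years.

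**The concern.** Read together, the first and third steps make baseline difference the entry rule for every covariate that is not demographic. The arms are formed by chance, so a test of baseline similarity can only pick up chance imbalance. It does not show which variables predict the outcome. The T0 score will usually be among the strongest predictors of the T1 score, yet under this rule it enters only when the arms happen to differ on it. With a 5% test that is about one trial in twenty for each outcome.

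Two things are at stake. Precision available from data already collected is mostly given up in the regression. And the six primary outcomes can end up with different models, each settled only once the data are seen.

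**Working it through.** **1. The plan's own figures.** The Power analysis section uses an independent-samples t-test "with a probability level of .05", without covariates. The normal approximation is n per arm = 2(1.960 + 0.842)² / d².

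- d = 0.5: 2 × 7.85 / 0.25 = 62.8, so 63. The exact noncentral t gives 63.8, so 64, as stated ("a desired statistical power of 0.8 will be 64").
- d = 0.2: 2 × 7.85 / 0.04 = 392.4, so 393. The exact value is 393.4, so 394, as stated ("between the 2 groups a total n of 788 (394 in each group) is required").

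A one-sided test would give 50 at d = 0.5, so the stated figures are two-sided. They are correct for an unadjusted comparison.

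**2. Inputs for the illustration.** The article gives no expected size for the randomised arms. The 220 per arm and 10% loss that it borrows from a cited study give 220 × 0.9 = 198. Also taken: d = 0.3 (used in the same section), two-sided 5%, SD = 1 and no demographic covariates. The T0–T1 correlation r is not in the article and is an assumption, shown as a range.

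**3. Power by analysis.** Power = Φ(d·√(n/2)/s − 1.96), with d·√(n/2) = 0.3 × √99 = 2.985. The residual SD s is 1 for T1 alone, √(1 − r²) for T1 adjusted for T0, and √(2(1 − r)) for change from T0. With two time points, change is the group-by-time test of a repeated measures ANOVA.

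| r | T1 alone | Change | T1 adjusted for T0 |
|---|---|---|---|
| 0.3 | 0.847 | 0.713 | 0.879 |
| 0.5 | 0.847 | 0.847 | 0.931 |
| 0.6 | 0.847 | 0.916 | 0.962 |
| 0.7 | 0.847 | 0.971 | 0.987 |

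For example, at r = 0.5: s = √0.75 = 0.866, 2.985 / 0.866 = 3.447, and Φ(1.487) = 0.931.

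At a given power, always including T0 multiplies the required n by about 1 − r². That is a reduction of 9%, 25% and 49% at r = 0.3, 0.5 and 0.7.

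**4. The rule as written.** The article does not say what counts as a difference. A baseline t-test with p < 0.05 is assumed. Simulation with 198 per arm and 10,000 runs per setting gave:

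| | r = 0.5 | r = 0.7 |
|---|---|---|
| Power at d = 0.2, never adjusting for T0 | 0.513 | 0.514 |
| Power at d = 0.2, adjusting only if T0 differs | 0.517 | 0.527 |
| Power at d = 0.2, always adjusting | 0.632 | 0.792 |
| Null rejection, adjusting only if T0 differs | 4.3% | 3.3% |

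A second simulation, with 153 per arm and d = 0.3 (8,000 runs per setting), shows the same pattern. Power under the conditional rule is about 0.76 at both correlations, against 0.86 and 0.96 when T0 is always included. Null rejection is about 4.7% and 3.8%.

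The rule is conservative for a simple reason. When T0 is balanced, the unadjusted standard error still counts T0 variation that is not in fact separating the arms.

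**The case against.** The strongest reply has four parts.

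- **Demographics are in the model regardless.** This stands. A reader might infer that the regression adds only variables found to differ, but the article's own wording rules that out. It also means that T1 alone is not quite the planned model. If demographics explained an assumed 10% to 20% of T1 variance, s² would be 0.9 to 0.8 and exact t power at 198 per arm would be 0.88 to 0.91. The further gain from T0 would then be smaller than in the table.
- **T0 is not wasted, because the repeated measures ANOVAs use it.** This stands in part. The ANOVA sentence does not mention the arm contrast. Read as a group-by-time test, it comes within 2 to 5 points of the adjusted analysis at r = 0.6 to 0.7. At r = 0.5 it gains nothing over T1 alone, and below that it does worse.
- **No false positives follow.** This stands. A reader might infer that data-driven covariate choice inflates type I error, but both simulations show rejection below 5%.
- **Covariate lists are commonly left to an SAP.** That would answer a missing list. It does not answer a rule that the article states, and the rule is a poor one.

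Two further inferences are tempting and lack support. Because entry depends on T0 frailty, one might blame regression to the mean for biasing the effect on frailty. It is equal in expectation in both randomised arms and cancels from the contrast, and the paragraph makes no within-arm effect claim from frailty change. One might also count the absence of stratified allocation as an error. The Randomization section is one condensed sentence, so its silence shows nothing, and stratifying is a design preference.

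**Conclusion.** The concern holds as a point of efficiency and pre-specification. The covariate rule in the effect regression ties adjustment to chance imbalance and leaves out, in most cases, the T0 score that the trial collects for every primary outcome. In the illustration, power rises from about 0.85 to about 0.93 at r = 0.5, or about 0.99 at r = 0.7, when T0 is always included. At r = 0.3 the rise is only to 0.88.

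These sizes rest on an assumed correlation, a borrowed arm size, no demographic covariates and, for the conditional rule, an assumed 5% entry test. The direction does not depend on those values: for any appreciable T0–T1 correlation, always adjusting is the more precise analysis. The stated sample sizes are not wrong, and the comparison of arms is neither biased nor anti-conservative.

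**What to change.** For each outcome, state one effect analysis in advance: regression of the T1 score on arm, the T0 score of the same outcome, the demographic variables already planned (naming those in the Additional measures section) and municipality. Fix all covariates before the data are seen, and delete baseline differences as a reason for adding one. Keep the baseline comparison of the arms as description. Make the repeated measures ANOVA supportive to the regression.

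The cost is wording plus three degrees of freedom per model beyond the planned demographics: one for the T0 score and two for the three municipalities. No new data are needed.

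### Apart from demographics, the covariates of the T1 regression depend on chance baseline differences between randomised arms, so the outcome's own T0 score is not guaranteed a place

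*Protocol article*

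**What the plan says.** Three statements in the protocol article bear on this.

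- Randomization: eligible participants are allocated "using computer-generated randomization to either the control or the experimental group".
- Analysis of the data, Effect evaluation, on comparing the arms: "Similarity of characteristics between the two groups will be assessed by means of independent sample t-tests or chi-square tests".
- The same paragraph, on the effect model: for each measure, "regression analyses will be performed with the T1 scores as the dependent variable". Research group is the independent variable of interest, and the covariates are "demographic variables and differences in baseline characteristics as co-variates".

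Demographic variables thus enter unconditionally. Any other baseline variable enters because the arms differ on it. The T0 score of the outcome is not named as a covariate, although Table 2 and the Data gathering section show that every outcome is measured at T0. The same paragraph also plans repeated measures ANOVAs for T0–T1 differences; these use the T0 scores but do not set the covariates of the regression.

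**The concern.** Between randomised arms, a baseline difference is a chance event. It carries no information about which variables are worth adjusting for. A covariate sharpens the treatment comparison because it predicts the T1 score, and the best predictor is usually the same measure at T0. A rule that admits covariates when the arms differ selects on the wrong property: it admits unimportant items that differ by luck and passes over strong predictors that happen to be balanced.

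Two things are at stake in the regression: precision that the T0 data could supply at no extra cost, and a model that is known before the results are.

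**Working it through.** **Inputs from the article.** Alpha: "with a probability level of .05". Main sample size: "effect size of 0.5 (medium) and a desired statistical power of 0.8 will be 64" per group. Small effect: "a total n of 788 (394 in each group) is required". Borrowed arm size: "By including 220 older adults in both the experimental and control group", with 10% loss to follow-up, so 220 × 0.9 = 198 analysed per arm.

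**Assumptions.** The article gives none of these: the T0–T1 correlation r (range 0.3 to 0.7), the number randomised (150 or 198 analysed per arm, 1:1), and an entry threshold of p < 0.05 for a baseline difference.

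**Step 1: reproduce the plan's figures.** A two-sided 0.05 t-test with 80% power needs 64 per arm at d = 0.5 and 394 at d = 0.2, as stated. With 198 per arm, power is 0.999 at d = 0.5 and 0.847 at d = 0.3, close to the 0.997 and 0.837 quoted from the cited study.

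**Step 2: how many variables the rule governs.** Table 2 lists 6 primary and 12 secondary outcomes measured at T0, so 18. Socio-demographic variables enter regardless and are not counted.

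- Chance differences expected: 18 × 0.05 = 0.9.
- Probability of at least one, if independent: 1 − 0.95^18 = 0.60.
- Counting household income as non-demographic gives 19 variables: 1 − 0.95^19 = 0.62.
- Probability that a given T0 score is left out: 1 − 0.05 = 0.95, however well it predicts T1.

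**Step 3: power.** Scale the outcome to SD 1. Let Zx be the standardised T0 imbalance and E an independent standard normal variable.

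- Unadjusted statistic: d√(n/2) + r·Zx + √(1 − r²)·E, with SE √(2/n).
- Adjusted for T0: d√(n/2)/√(1 − r²) + E, with SE √(2(1 − r²)/n).
- Rule: adjusted if |Zx| > 1.96, otherwise unadjusted.

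For n = 150 and d = 0.3, d√(n/2) = 0.3 × 8.660 = 2.598. Unadjusted power is Φ(2.598 − 1.96) = 0.738. With a fixed T0 covariate at r = 0.7, 2.598/0.714 = 3.638 and power is Φ(3.638 − 1.96) = 0.953. The rule was evaluated by simulation from these expressions:

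| Per arm | r | Rule | T0 fixed |
|---|---|---|---|
| 150 | 0.3 | 74% | 78% |
| 150 | 0.5 | 75% | 85% |
| 150 | 0.6 | 75% | 90% |
| 150 | 0.7 | 76% | 95% |
| 198 | 0.3 | 85% | 88% |
| 198 | 0.5 | 86% | 93% |
| 198 | 0.7 | 87% | 99% |

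A separate simulation fitting the regressions themselves (198 per arm, 4,000 trials per setting) gave 0.85 vs 0.87 at r = 0.3, 0.85 vs 0.93 at r = 0.5 and 0.86 vs 0.98 at r = 0.7.

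**Step 4: error rate and bias.** With d = 0, the rule rejects in 4.8% of trials at r = 0.3, falling to 3.6% at r = 0.7. In the regression simulation the mean estimate under the rule was within 0.003 of the true effect in every setting.

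These figures consider the T0 score alone. The demographic variables, which the plan always enters, would raise power in both columns if they predict T1, and the gap could then be smaller.

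**The case against.** **The entry rule is inferred.** The article does not say that a difference must be significant, and no sentence ties the t-tests to the regression. This stands: the 95% and the power figures depend on an assumed threshold. It does not rescue the plan, because differences judged by size or by eye would be just as data-dependent and harder to reproduce.

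**A covariate list belongs in the analysis plan.** The absence of a list is no finding. But the article does more than omit one: it states that baseline differences between the arms are a ground for adjustment, and that choice is the point here.

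**T0 scores are used elsewhere.** The repeated measures ANOVAs do use them, so the loss is confined to the regression. That regression is nevertheless the only analysis in the section that names research group as the independent variable of interest.

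**The loss may be small.** At r = 0.3 it is 3 to 4 percentage points, and low correlations are plausible because quality of life, community inclusion and ageing well in place are each measured by a single item. Also, the article's sample-size figures come from unadjusted t-tests, so the rule forgoes a gain and does not push power below what was planned.

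**Stronger readings that the document does not support.** A reader might infer that testing first and then adjusting inflates false positives or biases the effect. Step 4 shows neither: overall the rule is conservative. In the roughly 8% of trials with a T0 imbalance of |z| between 1.5 and 1.96, the null rejection rate is about 12% at r = 0.6. But any analysis that leaves T0 out behaves that way, so this is not a product of the testing. A reader might also count the socio-demographic variables among the candidates for selection; they enter in any case.

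**Conclusion.** The point holds as a weakness of the stated regression. Its non-demographic covariates are decided by chance differences between randomised arms, and the outcome's own T0 score has no assured place. The consequence is forgone precision and a model not known in advance.

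The size depends on quantities the article does not give. At d = 0.3, the power forgone is 3 to 4 points at r = 0.3, 12 points at r = 0.7 with 198 per arm, and 19 points at r = 0.7 with 150 per arm. This assumes a 0.05 entry threshold, equal allocation and no contribution from demographics. It should be corrected, but it does not threaten the validity of the comparison.

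**What to change.** In the Effect evaluation paragraph, replace the clause on baseline differences with a covariate set fixed before any T1 data are seen and used in every model: the T0 score of the outcome being analysed plus the demographic variables, listed by name. State that comparisons of the arms at baseline are descriptive and play no part in choosing covariates. Models with further covariates are labelled as sensitivity analyses.

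The cost is about two sentences of wording. No extra data, visits or participants are needed, since the T0 scores are already collected.
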